**Supplementary materials**

**Additional statistical methods**

*Estimating ethnicity by LSOA*

The data and analytical team in NHS England supplied the LSOA code based on the residential postcode of most women involved in this study. The estimated proportion of an ethnicity in each arm or service is calculated by weighing three elements and summing across LSOAs. First the composition of different LSOA in each arm or service, second the composition of different ethnicity in each LSOA, third the proportion of an arm or a service in the study.

For example, there were 48 women in this study from LSOA code E01028027, of which 13 (27%) were assigned to Timed/ Timed invitation strategy. According to census data,^1^ 66% women from this LSOA between age 50 and 74 years are of white ethnicity. We estimated (48 x 27% x 66% =) 8.54 women were allocated to Timed/Timed from LSOA E01028027 who are white. Sum this number across all LSOAs in a given arm will give the total number of women allocated to this arm in each ethnicity.

The definition of white and non-white adopted from the *Ethnic group classification 6a used in Census 2021*.^2^ Non-white incudes Asian, Black, Mixed and Other ethnic group, we had no women in the “does not apply” group, some women had missing LSOA linkage to the postcode from NHS Data Team and recorded as missing, excluded from the non-white ethnic group.

*Estimating attendance in each ethnicity by invitation strategy*

This is estimated using the LSOA code based on the residential postcode of most women involved in this study. Due to limitation of dataset, we could not estimate the probability for a woman being white for when she has attended in a given arm. As a result, estimate presented slightly underestimate attendance for the subgroup Timed/Timed and white, and overestimate for the subgroup Open/Open and non-white. The number of women who have attended within 90 days (180 days) who are white and assigned to Open/Open is estimated by:

Total number of women with LSOA recorded multiply by the probability of being assigned to Open/Open arm, then multiply by the probability of attend within 90 (180 days) using the assigned strategy, finally multiply by the probability of the women being white if she has attended.

*Use of letter print date when observing attendance over time*

When looking at the 90- and 180-day attendance over time amongst 4 invitation strategies since the initial appointment, we used 120- and 210-day attendance since the first invitation letter was printed, instead of using the period since the first appointment was offered. This was to account for the fact when women receive an open invitation, she can book an appointment and therefore attend earlier than the date originally assigned to the virtual clinic. i.e. virtual clinics tend to be 4 weeks since the letter sent, and a woman could call to have an appointment the next day from when the letter was received. When a letter was printed, it was expected to be sent the same or the next day and should be received within a week. As the date printed was around 30 days earlier than a virtual clinic could have been, this was added to 90 and 180 days when date of letter printed was used as the starting point for looking at attendance over time.

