**Supplementary Tables**

**Supplementary Table 1**: Breast screening uptake in 2021/22 and Index of Multiple Deprivation (IMD) quintile of selected services determined by the NHSBSP prior to the start of the study

| **Code** | **Service** | **Uptake^a^** | **IMD Quintile^b^** |
| --- | --- | --- | --- |
| FLO | Central and East London | 42% | 3 |
| EBA | North London | 54% | 2 |
| FBH | Outer NE London | 58% | 1 |
| MDU | Dudley, Wolverh. & SW Staffords. | 60% | 2 |
| DCB | Cambridge | 61% | 5 |
| CDO | Doncaster | 63% | 2 |
| LED | North and East Devon | 67% | 4 |
| ^a^ Year 2021/22 figure^3^  ^b^ 1 being the most deprived and 5 being the least deprived.. | | | |

**Supplementary Table 2**: Characteristics of women included in the services evaluation by NHSBSP service.

|  | Service name | | | | | | | | | | | | | |
| --- | --- | --- | --- | --- | --- | --- | --- | --- | --- | --- | --- | --- | --- | --- |
|  | Doncaster | | Cambridge | | North London | | Outer NE London | | Central and East London | | North and East Devon | | Dudley,Wolverh&  SW Staffords ^d^ | |
| Age (Mean, IQR) ^a^ | 60.0 | 54.0 – 65.0 | 54.4 | 50,0-59.0 | 59.4 | 55.0-64.0 | 58.8 | 54.0-64.0 | 58.5 | 54.0.63.0 | 59.1 | 55.0-65.0 | 58.4 | 52.0-64.0 |
|  |  |  |  |  |  |  |  |  |  |  |  |  |  |  |
| IMD (quintile) |  |  |  |  |  |  |  |  |  |  |  |  |  |  |
| 1: most deprived | 628.0 | (23.2%) | 83.0 | (3.6%) | 382.0 | (12.7%) | 1018.0 | (61.1%) | 514.0 | (22.1%) | 199.0 | (8.1%) | 1489.0 | (44.8%) |
| 2 | 422.0 | (15.6%) | 91.0 | (4.0%) | 780.0 | (25.9%) | 619.0 | (37.2%) | 1346.0 | (57.9%) | 306.0 | (12.4%) | 803.0 | (24.2%) |
| 3 | 564.0 | (20.8%) | 356.0 | (15.5%) | 743.0 | (24.7%) | 22.0 | (1.3%) | 304.0 | (13.1%) | 775.0 | (31.4%) | 525.0 | (15.8%) |
| 4 | 719.0 | (26.5%) | 679.0 | (29.5%) | 796.0 | (26.5%) | 2.0 | (0.1%) | 125.0 | (5.4%) | 616.0 | (25.0%) | 426.0 | (12.8%) |
| 5: least deprived | 359.0 | (13.2%) | 1051.0 | (45.7%) | 285.0 | (9.5%) | 0.0 | (0.0%) | 26.0 | (1.1%) | 542.0 | (22.0%) | 73.0 | (2.2%) |
| missing | 18.0 | (0.7%) | 41.0 | (1.8%) | 21.0 | (0.7%) | 4.0 | (0.2%) | 11.0 | (0.5%) | 30.0 | (1.2%) | 9.0 | (0.3%) |
|  |  |  |  |  |  |  |  |  |  |  |  |  |  |  |
| Prevalence and age |  |  |  |  |  |  |  |  |  |  |  |  |  |  |
| prevalent and <60 | 494.0 | (18.2%) | 1556.0 | (67.6%) | 762.0 | (25.3%) | 356.0 | (21.4%) | 805.0 | (34.6%) | 631.0 | (25.6%) | 1015.0 | (30.5%) |

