| incident and <60 | 771.0 | (28.5%) | 190.0 | (8.3%) | 821.0 | (27.3%) | 570.0 | (34.2%) | 545.0 | (23.4%) | 616.0 | (25.0%) | 827.0 | (24.9%) |
| 60+ | 1445.0 | (53.3%) | 531.0 | (23.1%) | 1424.0 | (47.4%) | 734.0 | (44.1%) | 974.0 | (41.9%) | 1221.0 | (49.5%) | 1483.0 | (44.6%) |
| missing | 0.0 | (0.0%) | 24.0 | (1.0%) | 0.0 | (0.0%) | 5.0 | (0.3%) | 2.0 | (0.1%) | 0.0 | (0.0%) | 0.0 | (0.0%) |
|  |  |  |  |  |  |  |  |  |  |  |  |  |  |  |
| Ethnicity ^b^ |  |  |  |  |  |  |  |  |  |  |  |  |  |  |
| Asian | 37.5 | (1.4%) | 71.1 | (3.1%) | 619.4 | (20.6%) | 143.0 | (8.6%) | 305.7 | (13.1%) | 37.8 | (1.5%) | 685.1 | (20.6%) |
| Black | 13.6 | (0.5%) | 22.7 | (1.0%) | 407.2 | (13.5%) | 331.8 | (19.9%) | 398.1 | (17.1%) | 7.8 | (0.3%) | 218.4 | (6.6%) |
| Mixed | 11.2 | (0.4%) | 17.5 | (0.8%) | 73.5 | (2.4%) | 21.5 | (1.3%) | 62.0 | (2.7%) | 15.0 | (0.6%) | 43.2 | (1.3%) |
| White | 2437.8 | (90.0%) | 1898.5 | (82.5%) | 1485.8 | (49.4%) | 1073.0 | (64.4%) | 1263.4 | (54.3%) | 2054.5 | (83.2%) | 2183.4 | (65.7%) |
| Other | 8.0 | (0.3%) | 14.3 | (0.6%) | 272.1 | (9.0%) | 31.7 | (1.9%) | 166.7 | (7.2%) | 11.8 | (0.5%) | 91.9 | (2.8%) |
| Missing ^c^ | 202.0 | (7.5%) | 277.0 | (12.0%) | 149.0 | (5.0%) | 64.0 | (3.8%) | 130.0 | (5.6%) | 341.0 | (13.8%) | 103.0 | (3.1%) |
| IMD, index of multiple deprivation; IQR, interquartile range   1. Age in years at first offered appointment. 2. Ethnicity is estimated based on the LSOA of women’s residential postcode, not of individual woman. See [appendix](#_Estimating_ethnicity_by) for further detail. 3. Women whose LSOA was unable to be linked to identify residential region. 4. Dudley, Wolverhampton, and Southwest Staffordshire. | | | | | | | | | | | | | | |

(a)

(b)

**Supplementary Figure 1** Proportion of women attending within 120 (a) and 210 (b) days since letter printed by invitation strategy. The red dotted line indicates the 70% uptake target as set by the NHS breast screening programme.

[figure not shown]

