| *imdquintile* | Index of Multiple Deprivation in quintiles | First, small area level index of multiple deprivation 2019 (*imddecile*) by linking *lsoacode (*2011) with IMD2019 data^2^, then derive from deciles to quintiles.   - 1 (least deprived) - 2 - 3 - 4 - 5(most deprived) |
| *ethnicity* | ethnicity (area level estimate) | Small area level ethnicity estimate derived by linking source data with the ethnicity data from Office for National Statistics site^3^ with *lsoacode* as identifier, for women from aged 50 and above, by linking LSOA with census data. Expect in 5 major categories:   - - 1, Asian or Asian British   - 2, Black or Black British   - 3, Mixed   - 4, Other ethnic groups   - 5, White |
| *ethnicity_white* |  | - - Derived from *ethnicity* as defined above.   - 1, white   - 0, non-white |
| *rurality* | Whether the screening site is rural or urban. | Derived by linking source data with the data from open geography portal, on ‘Rural Urban Classification (2011) of Lower Layer Super Output Areas in England and Wales”^4^, using *lsoacode* as identifier.   - - 0, rural   - 1, urban |
| *age_prev_status* |  | Derived from *ageatfoa* and *prevalentincidentstatus:*   - - 1, prevalent and under60,   - 2, incident and under60,   - 3, over60, and   If *prevalentincidentstatus* is missing, impute based on *ageatfoa.* |
| *firstarm* | Open invitation or timed appointment at the first invite. | Derived from *armname* |
| *secondarm* | Open invitation or timed appointment at the second invite. | Derived from *armname* |
| Note: when the *lsoacode* cannot be identified in the sourcedate during data linkage, resolve from checking the data file: LSOA (2011) to LSOA (2021) to Local Authority District (2022) lookup for England and Wales. ^5^ | | |

**NOTE:** The original source dataset should not be altered. Any modification to data extract MUST be saved to a separate file.

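### Supplementary Table 2 contradicts the stated reason for missing ethnicity: at least 1,132 women (6.4%) with no ethnicity estimate had an LSOA that linked to IMD

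*SAP*

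**What the plan says.** Three places in the document bear on this point.

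- **Reason for missing ethnicity.** The supplementary section on estimating ethnicity by LSOA states that "some women had missing LSOA linkage to the postcode from NHS Data Team and recorded as missing, excluded from the non-white ethnic group". Footnote c to the ethnicity block of Supplementary Table 2 describes the missing group as "Women whose LSOA was unable to be linked to identify residential region".
- **Derivation.** The SAP table under Data linkage and variable derivation obtains both IMD quintile and ethnicity from the variable *lsoacode*: IMD by linking the 2011 code to the 2019 indices, ethnicity by linking to census data. No other route to a woman's IMD quintile is given. A note below the table deals with a code that "cannot be identified in the sourcedate during data linkage, resolve from checking the data file", and names the LSOA 2011-to-2021 lookup as that file.
- **Use.** The ethnicity-specific attendance estimate starts from the number of women whose LSOA is on record. Area-level ethnicity is one of the two subgroup factors in the second primary objective, and the Subgroups section names it as a focus.

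**The concern.** If IMD and ethnicity come from the same code, a woman with no linkable LSOA should lack both, and a woman with an IMD quintile had a code that linked. The two missing rows of Supplementary Table 2 should therefore be close, yet they differ more than ninefold and nothing in the document explains why. Either the stated reason is wrong for most of the women concerned, or there is an undocumented step in the ethnicity linkage.

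At stake are the counts, and the women represented, in the ethnicity half of a primary objective. The reader also cannot tell which women form the base of the ethnicity attendance figures.

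**Working it through.** **Inputs, all from Supplementary Table 2.** Service order: Doncaster, Cambridge, North London, Outer NE London, Central and East London, North and East Devon, Dudley.

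- Ethnicity missing: "Missing ^c^ | 202.0 | (7.5%) | 277.0 | (12.0%) | 149.0 | (5.0%) | 64.0 | (3.8%) | 130.0 | (5.6" for the first five services and "341.0 | (13.8%) | 103.0 | (3.1" for the last two.
- IMD missing: "missing | 18.0 | (0.7%) | 41.0 | (1.8%) | 21.0 | (0.7%) | 4.0 | (0.2%) | 11.0 | (0.5" for the first five and "30.0 | (1.2%) | 9.0 | (0.3" for the last two.

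**Step 1: reproduce the table.** Summing the IMD block gives service totals of 2,710, 2,301, 3,007, 1,665, 2,326, 2,468 and 3,325, or 17,802 in all. The age and prevalence block gives the same totals; the ethnicity block agrees to within 0.1. All the printed missing percentages for ethnicity and IMD reproduce to one decimal.

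**Step 2: the gap.**

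- Ethnicity missing: 202 + 277 + 149 + 64 + 130 + 341 + 103 = 1,266 (1,266 / 17,802 = 7.1%).
- IMD missing: 18 + 41 + 21 + 4 + 11 + 30 + 9 = 134 (134 / 17,802 = 0.75%).
- Women with an IMD quintile but no ethnicity: at least 1,266 − 134 = 1,132 (1,132 / 17,802 = 6.4%).

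This minimum applies if every woman without IMD also lacks ethnicity. With no overlap the figure would be 1,266 (7.1%).

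**Step 3: by service** (ethnicity missing minus IMD missing, over the service total).

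| Service | Gap | Share of service | White share among women with an estimate |
| --- | --- | --- | --- |
| Doncaster | 202 − 18 = 184 | 6.8% | 97.2% |
| Cambridge | 277 − 41 = 236 | 10.3% | 93.8% |
| North London | 149 − 21 = 128 | 4.3% | 52.0% |
| Outer NE London | 64 − 4 = 60 | 3.6% | 67.0% |
| Central and East London | 130 − 11 = 119 | 5.1% | 57.5% |
| North and East Devon | 341 − 30 = 311 | 12.6% | 96.6% |
| Dudley | 103 − 9 = 94 | 2.8% | 67.8% |

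Doncaster, Cambridge and Devon supply 184 + 236 + 311 = 731 of the 1,132 (65%), but (2,710 + 2,301 + 2,468) / 17,802 = 42% of all women.

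**Step 4: the two possible bases.** Women with an LSOA on record, judged by the IMD row: 17,802 − 134 = 17,668. Women with an ethnicity estimate: 17,802 − 1,266 = 16,536.

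**Step 5: effect on the ethnic mix.** The White counts sum to 12,396.4, and 12,396.4 / 16,536 = 75.0%. Assume all 1,132 are recovered and each has her service's White share from step 3. The sum of gap × White share is then about 940 White women, leaving about 192 non-White, and (12,396.4 + 940) / 17,668 = 75.5%. The assumption matters: the share would be 12,396.4 / 17,668 = 70.2% if none of the recovered women were White, and (12,396.4 + 1,132) / 17,668 = 76.6% if all were.

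**The case against.** The subtraction is not in dispute. The case on the other side concerns what may be built on it, and most of that case stands.

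- **Cause.** A reader might infer that the gap is a mismatch between 2011 and 2021 LSOA codes, that all 1,132 women are recoverable, and that the loss was needless. The documents do not settle this. The supplementary methods tie only the White/non-White classification to Census 2021. For area composition they cite a reference listed as mid-2019 population estimates on April 2020 geography, and the SAP's own ethnicity reference gives no census year. A code mismatch is likely, but it is an inference.
- **Whether the lookup was used.** The SAP prescribes it, and nothing says that it was skipped. The 1,266 could be what remained after it was applied. That would leave footnote c just as inconsistent with the IMD row.
- **Whether the women are left out of the attendance estimates.** Read fairly, the first quotation says that unlinked women were not counted as non-White by default, which is proper. The attendance formula starts from women with an LSOA on record; taken literally, that includes the 1,132. Their exclusion from attendance cannot be asserted. What stands is that the base is ambiguous.
- **Selection by ethnicity and uptake.** The pattern is looser than it first looks. Among women with an estimate, every service is majority White. Cambridge and Dudley differ by one point in 2021/22 uptake (61% and 60%), yet their gaps are 10.3% and 2.8%. Weighting the uptake in Supplementary Table 1 by service, and assuming equal uptake for both groups within a service, recovery would move average uptake from 59.2% to 59.3% for White women and leave it at 53.9% for non-White women.
- **Bias between strategies.** A reader might also infer biased arm comparisons. Missingness is shown by service, not by arm, and allocation used identifier digits, which gives no evident route for area linkage to differ by arm.

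The GP-registration weighting in the caption of Supplementary Figure 2 does not answer the point: it concerns centre-level IMD scores, not the quintile counts in Supplementary Table 2.

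**Conclusion.** The explanation given for missing ethnicity cannot be right for at least 1,132 of the 1,266 women, on the document's own figures. This rests on one premise that the SAP itself states: a woman's IMD quintile comes only from her LSOA code. The shortfall is 6.4% of the study, occurs in all seven services and is uneven between them. It leaves two candidate denominators for the ethnicity attendance estimates.

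The consequence is limited. Only the ethnicity half of the second primary objective is touched, since the IMD half loses 0.75%. The overall White share moves by about half a percentage point if recovered women resemble their service. It remains worth correcting: the stated reason is wrong, the ethnicity counts would change, and the base of a primary-objective subgroup is undefined.

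**What to change.** 1. Apply the LSOA 2011-to-2021 lookup named in the note under Data linkage and variable derivation to every *lsoacode* that has no ethnicity match.
2. Record ethnicity as missing only where the code is absent or still unmatched after that step.
3. Report the remaining missing women by arm, with the true cause. If the cause proves not to be code versions, say what it is.
4. State one denominator and use it for both the ethnicity counts and the ethnicity attendance estimates.
5. Rerun the ethnicity rows of Tables 1, 2 and 6 and of Supplementary Table 2, and Supplementary Figure 2.
6. Correct the sentence in the supplementary methods and footnote c.

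The cost is one merge with a file that the plan already cites, a rerun of the ethnicity outputs and two text corrections. No new data are needed. If every woman with an IMD quintile is matched, missing ethnicity falls from 1,266 (7.1%) to at most 134 (0.75%); how far it actually falls depends on the cause.

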# Study details

## Objectives

The primary objectives are to evaluate:

1. the effect of different combinations of timed appointments and open invitations on attendance in the NHS Breast Screening Programme; and

2. the effect as above in subgroups defined by index of multiple deprivation (IMD), and area-level summaries of ethnic diversity.

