## Subgroups

Subgroups for reporting are below, further details are in [section 3.2.1](#source_data_variable) and [section 3.2.2](#derived_variables):

1. IMD (quintile):
   - 1: most deprived
   - 2
   - 3
   - 4
   - 5: least deprived
2. Ethnicity(area-level):

- White
- Non-white

1. Combination of prevalent/incidence screen and binary age categories:
   - Prevalent and under 60
   - Incident and under 60
   - Age 60 and over
2. Screening services:
   - Central and East London (pilot area where the study was first run)
   - Outer Northeast London
   - North London
   - Cambridge
   - North and East Devon
   - Doncaster
   - Dudley, Wolverhampton, and Southwest Staffordshire
   - East Lancashire
3. Rurality of the screening site:
   - Rural
   - Urban
4. Mobility of the screening clinic:
   - Static, e.g. hospital
   - Mobile, e.g. van

Our focus lies in the first two subgroups, IMD quintiles and the area-level ethnicity.

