## Primary analysis

For the primary analysis a hierarchical approach will be used for testing at the 5% level. In the first instance, a global likelihood ratio test on 3 degrees of freedom will be applied to assess the significance of a difference in any direction among the groups overall. Also, a four-way comparison with OO as the reference category.

To account for multiple comparisons, null hypotheses (no difference in 90-day screening attendance between arms) will be tested in the following order:

(1) Timed Timed (TT) vs Open Open (OO).

(2) TT vs OT.

(3) TO vs OT.

(4) TT vs TO.

(5) OT vs OO.

Testing will only proceed if the preceding hypothesis was rejected at the 5% level (p-value <0.05).

Independently of significance test results, both overall and for specific subgroups, we will report the most successful group in terms of 90-day attendance.

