## Subgroup analysis

The estimated attendance by 90 days and 180 days by arm will be reported by subgroups (with 95%CIs for each endpoint).

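### The formula for attendance by ethnicity forces the same relative effect of invitation strategy in White and non-White women, so the ethnicity rows of Table 6 cannot show whether it differs

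*SAP*

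**What the plan says.** Primary objective 2 in the SAP (Objectives) is to evaluate "the effect as above in subgroups defined by index of multiple deprivation (IMD), and area-level summaries of ethnic diversity". The Subgroups section adds: "Our focus lies in the first two subgroups, IMD quintiles and the area-level ethnicity".

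The supplementary section Additional statistical methods explains how the ethnicity rows are built. The denominator for each arm comes from census shares: the women an LSOA contributes to the arm are multiplied by that LSOA's White share, and "Sum this number across all LSOAs in a given arm will give the total number of women allocated to this arm in each ethnicity". The numerator starts from all women with an LSOA and multiplies by the probability of being in the arm. The text continues "then multiply by the probability of attend within 90 (180 days) using the assigned strategy", and "finally multiply by the probability of the women being white if she has attended". The reason given for a last factor that is not specific to the arm is that "we could not estimate the probability for a woman being white for when she has attended in a given arm".

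The same paragraph acknowledges a slight underestimate for White women in TT and a slight overestimate for non-White women in OO. It gives no size. It does not say what the formula does to the comparison of strategies between ethnic groups.

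**The concern.** Only one factor in the numerator carries information about how strategy affects attendance, and it is the rate for the whole arm. A formula that applies one overall effect to both ethnic groups will return that effect in both. A reader of Table 6 would see parallel results in White and non-White women and could take them as evidence that the strategies work alike. In fact the method would have imposed the agreement. This is one of the two subgroups on which the SAP says it focuses.

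**Working it through.** **Inputs from the SAP.** Planning rates are 65% and 73% (Sample Size Justification). I reproduce the 524 per group: pooled variance, no continuity correction, two-sided 5%, 80% power. The worked LSOA example also reproduces: 48 x 0.27 x 0.66 = 8.55 against 8.54 stated, a rounding difference. Summing Supplementary Table 2 over the seven services gives 12,396.4 White and 4,139.6 non-White of 16,536 women with an ethnicity estimate. The White share is 12,396.4/16,536 = 75.0%. A further 1,266 of 17,802 women (7.1%) have no estimate.

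**Algebra.** Let N be the women with an LSOA, p_a the proportion in arm a, r_a the attendance in arm a, w the White share among attenders (not by arm), and W_a the White share of women allocated to arm a. The SAP writes out the White case; I take 1 - w for non-White.

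- White rate in arm a = (N p_a r_a w)/(N p_a W_a) = r_a w/W_a
- Non-White rate in arm a = r_a (1 - w)/(1 - W_a)
- White TT:OO ratio = (r_TT/r_OO) x (W_OO/W_TT)
- Non-White TT:OO ratio = (r_TT/r_OO) x (1 - W_OO)/(1 - W_TT)

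The factor w cancels, so this does not depend on how w was computed, provided it does not vary by arm. If W_a is equal across arms, as the allocation intends, both ratios are r_TT/r_OO.

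**Numbers.** I hold overall attendance at OO 65% and TT 73% (ratio 0.73/0.65 = 1.123) and the White share at 75.0% in every arm. Assumptions: four equal arms, a White rate of 68% in OO, and TO and OT spaced evenly between OO and TT. The non-White rate in OO is then (0.65 - 0.7497 x 0.68)/0.2503 = 56.0%.

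| True TT-OO difference, White / non-White (points) | True ratio, White / non-White | Formula ratio, White / non-White | Formula difference, White / non-White (points) |
|---|---|---|---|
| +8 / +8 | 1.118 / 1.143 | 1.123 / 1.123 | 8.3 / 7.0 |
| +4 / +20 | 1.059 / 1.357 | 1.123 / 1.123 | 8.1 / 7.7 |
| +10 / +2 | 1.147 / 1.036 | 1.123 / 1.123 | 8.5 / 6.6 |
| 0 / +32 | 1.000 / 1.570 | 1.123 / 1.123 | 7.9 / 8.3 |

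For the second row w = 0.7605. White TT is 0.73 x 0.7605/0.7497 = 74.1% and White OO is 65.9%. The non-White rates are 69.8% and 62.2%.

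**Chance imbalance.** The two ratios can separate only if W_a differs between arms. With 16,536/4 = 4,134 women per arm and an assumed SD of LSOA White share of 0.15 to 0.30, the 95% limit for the difference in W between two arms is 1.96 x SD x sqrt(2/4,134), or 0.006 to 0.013. That moves the White ratio by about 1% to 2% and the non-White ratio by about 3% to 5%. Neither shift reflects attendance.

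**Is an arm-specific figure possible?** The Variables for analysis section lists LSOA code, arm, attendance and screening date, and Preparing data for analysis builds one row per woman. The worked example already counts one LSOA's women by arm. IMD quintile is derived from LSOA code, and Table 6 reports attendance by arm within quintile, which needs the same linkage.

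**The case against.** The strongest reply is that the Data dictionary contains no individual ethnicity. The true probability that an attender in a given arm is White cannot be obtained without assuming how attendance varies by ethnicity within an LSOA. That stands. A reader might infer that the stated data limitation is unreal, and the SAP does not support this. What the data do allow is an arm-specific analysis at area level, which is how the objective is worded.

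Second, the SAP never says how the White share among attenders was calculated. The two bias directions it states are odd under a value pooled over arms, since they need the share in both TT and OO to exceed the pooled value. The mechanism is therefore partly inferred. The conclusion is not: any value common to all arms cancels. If the White share of all women were used instead, both groups would simply receive the arm's overall rate.

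Third, Supplementary Figure 2 sets attendance by service and strategy against each service's non-White percentage and does not use this formula. Among linked women that percentage runs from about 3% (Doncaster, 70 of 2,508) to 48% (North London, 1,372 of 2,858). It is some evidence on area diversity, but it covers seven services that differ in much else, with no test described.

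Fourth, the primary comparison of arms is untouched and the subgroup output is descriptive. This is true, but the ethnicity question sits under a primary objective.

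A reader might also fold in how subgroups are reported generally, such as the lack of an interaction test or the naming of the most successful arm. Those are separate matters, independent of this formula.

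**Conclusion.** The concern holds for the ethnicity part of primary objective 2. The formula makes the relative effect of strategy equal in White and non-White women, apart from chance imbalance in White share, so the ethnicity rows of Table 6 cannot show relative effect modification. This rests on the last factor being common to all arms, as the text indicates, and on the allocated women in each ethnic group serving as the denominator. The SAP's description of a slight bias in two cells does not convey this.

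Three stronger readings are not supported:

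- That objective 2 as a whole cannot be answered. IMD is attached to each woman through her LSOA and does not pass through the formula.
- That the bias must be large. It depends on unknown true effects: nil if the true ratios are equal, small in the +8/+8 case, large in the 0/+32 case. The subgroup rates used here are assumptions.
- That all effect modification is erased. Only the relative effect is forced equal. Absolute differences can still differ because the baselines differ, though they may rank the groups wrongly, as in the +4/+20 case.

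**What to change.** Replace the formula with an individual-level modified Poisson model (Poisson with robust variance, as in Primary endpoint methods). Model 90-day attendance on arm, LSOA proportion non-White as a continuous term, and their interaction. Standard errors may be clustered on LSOA if wished. Report the interaction test and the arm effects with 95% CIs at a low and a high non-White share fixed in advance. Word the result as an effect by area composition.

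A weaker fallback is to sum the LSOA White share over actual attenders in each arm and divide by the same sum over all women allocated to that arm. It lets the ratios differ but remains attenuated. In a simulation with assumed inputs (16,500 women, 1,500 LSOAs, mean White share 0.79, true effects +4 and +22 points), the true ratios were 1.06 and 1.40. The fallback gave 1.10 and 1.19, and the SAP formula 1.12 and 1.12.

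If the formula is kept, state beside it and under Table 6 that the ethnicity rows cannot show whether the relative effect differs by ethnicity, and drop the description of the bias as slight.

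The cost is a few model runs on data already held. The result will describe areas and not individual women, its CI will be wider, and it will leave out the roughly 7% of women without LSOA linkage.
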